### Study setting

MCSP is working in selected health facilities in Ebonyi and Kogi States in Nigeria to improve the quality of care received by mothers and newborns on the day of birth using high-impact evidence-based lifesaving interventions. Nigeria with a population of 185.7million has 6 geopolitical zones of which Ebonyi with a population of 2.79 million is in the South-east and Kogi with a population of 4.3million is located in the Northcentral zone (please see Fig. 1). At the time of the study, MCSP was supporting 120 health facilities, of which 60 will be selected to be part of the study.

**Fig. 1 Fig1:**
[figure not shown]
Geographical locations of project States

### Eligibility criteria

#### Health facilities

Selection of health facilities will be from the 120 supported by MCSP in the two states in all three senatorial geopolitical zones per State and will include all three levels of healthcare delivery namely primary (primary health care/private clinics), secondary (general/mission) and tertiary.

#### Service providers

Individual study participants will be drawn from those providing maternal and newborn health in the selected health facilities in the two states. Participating health workers will include doctors, nurses, midwives and community health extension workers. The service providers should have spent at least 6 months in maternal and/or newborn care services, and should be available to participate in the training from the beginning to the end (12-month period).

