### Randomization

The unit of randomization will be the health facility. All 60 facilities will be divided into 9 strata by 3 geopolitical zones and by level of healthcare delivery; each stratum is randomized to either control or intervention using randomly permuted blocks in ratio of 1:1 to achieve balance in type of facility and location by treatment arm. Health facilities will be matched prior to randomization and will be grouped as either receiving simulation-based LDHF/m-Mentoring or traditional training. As skilled birth attendants are few in the health facilities, all health providers working in maternity or newborn units who meet the inclusion criteria will be selected from the randomized health care facilities. Arm 1 will include birth attendants who will be trained using LDHF approach while arm 2 will be those who will be trained using TRAD approach.

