### Sample size

We will calculate the average number of providers who will be included from each of the 60 facilities (or 30 facilities in each arm) using a test of two proportions for a binary indicator of a present competency score. Competency will be assumed at a score of 80% or higher score on both the knowledge and skills assessments. We assumed that the proportion of competent providers will be 50% in the control group. The goal is to have at least 80% power to reject a null hypothesis that the proportions are equal across the two arms against the alternative hypothesis of a minimum effect size of 20 percentage point difference in proportions of competent providers. The test of hypothesis will be performed at 0.05 level of significance. Sample size was calculated using PASS statistical software [14]. Since some facility-level factors that are shared by the providers working in the same facility can influence the competency level, we will assume 0.05 within facility correlation of competency levels across providers in a given health facility**.** Assuming that an average of four (04) service providers sampled per health facility, a total of 240 providers across the two groups will be needed so that there will be at least 80% power to detect a 20 percentage point difference in competence level between the two arms (assessment at 3 months) at 0.05 level of statistical significance. The final sample size will be 300 or 150 providers per study arm to account for potential 20% drop-out at the time of post-training assessment. The participants for each facility will include the maternity unit head wherever possible and two others; to ensure the other team members receive the necessary support they need to practice the competencies. Study participants will be administered a single survey comprised of modules on characteristics, knowledge, and costs incurred in addition to a competency assessment prior to training and at three time points following training (end of training day, 3, 12 months post-training).

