### Training approach 1 and data collection: Simulation-based LDHF/m-mentoring training of participants - group 1 or intervention group

The training for the LDHF arm will be for the entire team of service providers available at the health facility, but only those who will meet the study inclusion criteria will be assessed. After oral consent is obtained, the participants will take pre-training assessments consisting of MCQs and OSCEs through use of manikins, to assess their baseline knowledge and skills. The MCQ contains a set of multiple choice questions to test trainees’ knowledge. OSCE involves the use of validated checklists to evaluate trainees’ demonstration of clinical skills to ensure that each step is correctly and completely carried out. The assessments will test their knowledge and skills on conduct of normal delivery, active management of the third stage of labor (AMTSL), neonatal resuscitation, case management of pre-eclampsia and eclampsia (PEE) and management of PPH (e.g. manual removal of placenta, internal bimanual uterine compression and compression of the abdominal aorta). The training will be divided into two “low-dose” training courses of 4 days each, with additional time for assessment as needed and will be conducted at the health facilities using the adapted basic emergency obstetrics and newborn care (BEmONC) package repeated after 1 month. The training techniques will be modified to shift the emphasis to practice. The time spent on lectures will be reduced and time spent on hands-on practice will be increased. The Peer Practice Coordinators (PPCs) will receive technical update in LDHF including the use of session plans, case scenario and MamaNatalie/NeoNatalie models to conduct simulation practices. At the end of the four-day training, the participants will undergo an immediate post-training assessment which includes MCQs and OSCEs. The questions answered correctly and procedure done competently is scored over a total of 100%. A test score of ≥80% is accepted as level of competence. The pre-training and immediate post-training assessments results will be compared. During the one-month intervals between training courses, health care providers will have the opportunity to practice what they learned and reinforce their competencies through high-frequency simulation-based practices of 2–3 times weekly. The PPCs will complete the practice log. In addition to the simulation exercises, all the trained providers in the LDHF arm will participate in mobile Mentoring (mMentoring), which consists of receiving weekly reminder messages and quiz questions on the topics reviewed via SMS messaging. Also the PPCs will receive structured, monthly half-hour mentoring calls from a trainer/master mentor that provide remote support, answering questions, providing guidance and reinforcing key messages. Skills and knowledge assessments will be done at three time points post-training (immediate post training day, at 3 months 12 months). Trainees’ satisfaction with the simulation-based LDHF/m-Mentoring training approach will also be determined using satisfaction (quantitative) survey.

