### Training approach 2 and data collection: Traditional group training of participants – Group 2 or control group

The traditional training approach will consist of 8 days of lectures with practice sessions on simulators, off-site the participants’ workplace, usually in a hotel. Oral consent will be obtained, the participants will take pre-training assessments consisting of MCQs and OSCEs through use of manikins, to assess their baseline knowledge and skills respectively. The assessments will test their knowledge and skills on conduct of normal delivery, AMTSL, neonatal resuscitation, case management of PEE and management of PPH (e.g. manual removal of placenta, internal bimanual uterine compression and compression of the abdominal aorta). This group then receives lectures and practice sessions on conduct of normal delivery, AMTSL, neonatal resuscitation, case management of PEE and management of PPH. The Nigerian BEMONC package and clinical observation checklists are used during the training sessions. The group-based training approach will include training sessions consisting of 8 days of lectures and fewer practice sessions using manikins (MamaNatalie/NeoNatalie) offsite and not at the trainees’ place of work. Table 1 outlines the basic similarities and difference between the two groups. At the end of the eight-day training, the participants will undergo an immediate post-training assessment which includes MCQs and OSCEs. As described among arm 1, the questions answered correctly and procedure done competently will be scored out of a total of 100%, assessments results will be compared and trainees satisfaction survey will be conducted.

**Table 1 Tab1:** Comparison of the Simulation-based LDHF and Group-based study arms

Parameters of the interventions received	Simulation-based LDHF Arm	Group-based Arm
Training covers BEMONC	Yes	Yes
Training is onsite	Yes	No
More frequent practise sessions using manikins during training	Yes	No
Post-training Practise Sessions with manikin in facility	Yes	No
Presence of PPCs	Yes	No
Use of mobile phone for post-training support	Yes	No
All courses divided into two phases which are 1 month apart	Yes	No

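### Providers appear to be enrolled after their facility is allocated, under an availability rule whose meaning depends on the arm, so the two arms can admit different staff

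*Protocol article*

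**What the plan says.** - **Unit and order.** Under Randomization, "The unit of randomization will be the health facility". The same section takes every provider in the maternity or newborn unit "who meet the inclusion criteria will be selected from the randomized health care facilities", because skilled attendants are few.
- **Eligibility.** Under Service providers, a provider needs at least 6 months in maternal or newborn care and "should be available to participate in the training from the beginning to the end (12-month period".
- **Consent and baseline.** In the LDHF training section: "After oral consent is obtained, the participants will take pre-training assessments". In the TRAD training section: "Oral consent will be obtained, the participants will take pre-training assessments".
- **What must be attended.** LDHF is on-site for the whole team, in two courses of 4 days each, followed by in-facility practice and mobile mentoring. TRAD is 8 days away from the workplace.
- **Who is selected, second statement.** Under Sample size: "The participants for each facility will include the maternity unit head wherever possible and two others".
- **Blinding.** Study design describes it for the independent skills and knowledge assessors, and for nobody who identifies or enrols providers.
- **Attrition.** The target rises to 300 "to account for potential 20% drop-out at the time of post-training assessment". Inferential analysis adds adjustment for baseline imbalance and, above 5% missing data, multiple imputation under missing at random.

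**The concern.** Randomising facilities balances facilities. It balances the providers inside them only if who enters the study does not depend on the arm. If staff are listed and consented once the allocation is known, and must be available for a training whose format the allocation determines, the eligibility rule itself can select differently by arm.

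The Background supplies the mechanism. It says that off-site training reaches only a few staff per site and takes them out of practice, and it credits facility-based training with less absenteeism. Staff who can leave for 8 days may differ in seniority, cadre or skill from staff who can attend at work. The 3-month competency comparison would then mix the training effect with a difference in who was assessed.

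**Working it through.** **The plan's sample size.** Inputs from the Sample size section: 50% competent in control, a 20-point difference (so 70%), alpha 0.05 (taken as two-sided), power 80%, intra-facility correlation 0.05, 4 providers per facility.
- Design effect: 1 + (4 − 1) × 0.05 = 1.15.
- Two-proportion test with continuity correction: 103 per arm; 103 × 1.15 = 118.45, which rounds up to 30 facilities × 4 = 120 per arm, or 240 in total. Without the correction: 93 × 1.15 = 107 per arm, and 240 then gives 84.4% power.
- Drop-out: 240 / (1 − 0.20) = 300.

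Both stated figures, 240 and 300, reproduce.

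**How many providers per facility.** 300 / 60 = 5 enrolled, and 5 × 0.8 = 4 evaluable, so four and five agree. The unit head and two others gives 3, or 3 × 60 = 180 in total, below both 240 and 300. The take-all rule sets no fixed number. Three per facility and take-all cannot both hold where more than three providers are eligible, and only the first leaves someone to choose.

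**How far selection could move the contrast (all inputs assumed).** Take 100 eligible staff per arm, 20 of whom cannot be released for 8 days. Suppose TRAD enrols none of the 20 and LDHF enrols 15.
- Hard-to-release share: LDHF 15 / (80 + 15) = 0.158; TRAD 0.
- Shift in the contrast = 0.158 × competence gap. A gap of 10 points gives 1.6; a gap of 30 points gives 4.7.
- The sign depends on whether those staff are more or less competent than the others, which the document does not say.

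A second set of assumptions: one arm misses 20% of its staff, whose competence is 30% against 50% overall. The rest have (0.50 − 0.20 × 0.30) / 0.80 = 0.55, a shift of 5 points. If it misses 10%, the rest have (0.50 − 0.10 × 0.30) / 0.90 = 0.522, a shift of 2.2 points.

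**What such shifts would do.** With 120 evaluable per arm, the effective number is 120 / 1.15 = 104.3. With no true effect and 50% competent, the standard error of the difference is √(2 × 0.25 / 104.3) = 0.069.

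| Assumed shift (points) | Two-sided type I error (nominal 5%) | Power for 50% vs 70% if the shift is against LDHF |
|---|---|---|
| 0 | 5% | 84.4% |
| 2 | 6.0% | 75.7% |
| 5 | 11.2% | 59.3% |
| 10 | 30.3% | 30.5% |

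The table shows sensitivity. It does not estimate what will happen in this trial.

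**The case against.** - **Take-all rule.** Enrolling every eligible provider is a recognised protection and removes most recruiter discretion. This stands as a partial safeguard. It does not remove the arm-dependent availability test inside the eligibility rule, and the unit head plus two others competes with it.
- **The sequence is inferred.** Randomised facilities may simply name the 60 trial sites, and placing consent under arm headings may be only layout. A condensed article may leave enrolment logistics to the full protocol. This stands as a limit on certainty: the order is the natural reading and nothing contradicts it, but it is not stated.
- **Equal course time.** Two courses of 4 days and one of 8 days ask for the same number of course days, and LDHF adds practice 2–3 times weekly. This is right. The difference lies in being released from the workplace, not in duration.
- **Planned adjustment and imputation.** Comparing pre-test scores and adjusting for imbalance would reduce a measured difference. They cannot address unmeasured differences, and imputation covers only providers who were enrolled.
- **The 12-month wording.** A reader might infer that it contradicts the 20% drop-out allowance and breaks intention-to-treat by making later leavers ineligible. The document does not support that. Read as expected availability at enrolment, the criterion, the allowance and the imputation plan are consistent, and nothing says leavers are removed. The wording sits badly with the allowance only if it is applied retrospectively.

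**Conclusion.** The point holds as a risk of bias written into the enrolment rules. Eligibility is tied to availability for a training whose setting differs by arm, enrolment appears to follow allocation, no blinding is described for those who enrol, and two statements of who is selected conflict. A reader might go further and conclude that the arms will differ in staff. The document does not show that: its take-all rule works against it, and no enrolment data are given.

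The size is unknown. The 1.6 to 4.7 points rest on assumed release and enrolment rates, including the extreme case of no hard-to-release staff in TRAD, and on an assumed competence gap. They are small against the 20-point target, but shifts near 5 points would roughly double the type I error.

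**What to change.** 1. Draw up and freeze the roster of eligible providers at all 60 facilities before the allocation is disclosed. The trial was registered retrospectively, so enrolment may already have begun; in that case report eligible against enrolled providers by arm and state the order in which allocation, listing and consent took place.
2. Reconcile the Randomization and Sample size sections on who is selected. If not all eligible providers are taken, state the rule for choosing the others.
3. Reword the availability criterion to no transfer, leave or retirement known at enrolment, independent of training format.
4. Analyse every rostered, consented provider in the facility's arm whether or not training was completed, with later leavers treated as missing outcomes under the existing imputation plan.

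**Cost.** Rosters must be in before the allocation list is released; the rest is wording and one reporting table. Pre-testing before disclosure would be better still, but it means MCQs and OSCEs at all 60 sites ahead of training and is not required.

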### Randomization

The unit of randomization will be the health facility. All 60 facilities will be divided into 9 strata by 3 geopolitical zones and by level of healthcare delivery; each stratum is randomized to either control or intervention using randomly permuted blocks in ratio of 1:1 to achieve balance in type of facility and location by treatment arm. Health facilities will be matched prior to randomization and will be grouped as either receiving simulation-based LDHF/m-Mentoring or traditional training. As skilled birth attendants are few in the health facilities, all health providers working in maternity or newborn units who meet the inclusion criteria will be selected from the randomized health care facilities. Arm 1 will include birth attendants who will be trained using LDHF approach while arm 2 will be those who will be trained using TRAD approach.

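### Nine randomisation strata do not fit two States with three zones each and three levels of care, so State is left out of the allocation and balance in location is not secured at State level

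*Protocol article*

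**What the plan says.** Under Health facilities (Eligibility criteria), the sites are chosen "in the two states in all three senatorial geopolitical zones per State", and the selection "will include all three levels of healthcare delivery namely primary", secondary and tertiary. Study setting adds that Nigeria "has 6 geopolitical zones of which Ebonyi with a population of 2.79 million is in the South-east", with Kogi in the Northcentral zone.

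Under Randomization, the article makes four statements about the allocation:

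- Unit: "The unit of randomization will be the health facility".
- Strata: "All 60 facilities will be divided into 9 strata by 3 geopolitical zones and by level of healthcare delivery; each stratum is randomized".
- Method: "using randomly permuted blocks in ratio of 1:1", with the declared purpose of balancing the arms on facility type and location.
- Matching: "Health facilities will be matched prior to randomization". No pairs or matching variables are given.

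On the analysis side, Descriptive analysis checks balance on facility location and level of care, among other characteristics. Inferential analysis then adjusts for provider and facility characteristics that turn out imbalanced and may correlate strongly with the scores. Neither section names State or commits to the stratification factors as model terms.

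**The concern.** The number of strata does not agree with the geography given two sections earlier. If the count of nine is right, a zone of Ebonyi and a zone of Kogi must share a stratum. A block can then be balanced between arms while its intervention facilities come mostly from one State. State is the coarsest location factor in the trial, and the two States lie in different national zones, so location balance is not assured at the level where a reader would first look for it.

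The description of the procedure is also unsettled. Permuted blocks within strata and matching before randomisation are different designs, and the article names both without saying which one produces the allocation. A reader cannot reconstruct the scheme or know which design factors the analysis should carry.

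**Working it through.** **1. Reproducing the stated count.** Taking the Randomization section alone, 3 zones x 3 levels = 9. This matches the text.

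**2. Count from the eligibility section.** 2 States x 3 zones per State x 3 levels = 18 possible cells. Some may be empty (tertiary facilities, for example), so 18 is a maximum. Mean facilities per cell: 60/18 = 3.3, against 60/9 = 6.7 with nine strata.

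**3. Other ways to reach nine.**
- National zones: each State lies in one, so 2 zones x 3 levels = 6 strata.
- Nine strata within each State: this gives 18 in total and conflicts with the statement that all 60 facilities go into 9.
- Zones pooled across States: 3 x 3 = 9. Of these readings, only this one gives nine, and it leaves State out.

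**4. How uneven State could be.** Inputs: 60 facilities, 30 per arm (Sample size). Assumption, not in the article: 30 facilities in each State. As an approximation, treat State as unconstrained, so that the number X of one State's facilities in the intervention arm is hypergeometric (60 facilities, 30 in that State, 30 drawn).
- Mean = 30 x 30/60 = 15.
- SD = sqrt(30 x 0.5 x 0.5 x 30/59) = sqrt(3.81) = 1.95.
- P(X ≤ 12) = P(X ≥ 18) = 0.098, so P(18:12 or worse) = 0.196.

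The result depends little on the assumed State split. The probability that X departs from its mean by 3 or more is 0.187 for a 36/24 split of facilities between States and 0.170 for 40/20.

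**5. The same question with blocking in place.** A simulation of 20,000 runs, assuming 30 facilities per State and a 70/25/5% mix of primary, secondary and tertiary, with permuted blocks of 2 or 4, gives the difference between arms in one State's facility count:

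| | 9 strata pooled over State | 18 State-specific strata |
|---|---|---|
| Mean absolute difference | 3.2 to 3.3 | 1.4 to 1.9 |
| 95th percentile | 8 (19 v 11) | 4 |
| Difference of 6 or more | 22 to 23% | 1 to 4% |

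Blocking within nine pooled strata therefore does not control State; the 22 to 23% is close to the 20% from step 4.

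**6. What an 18:12 split would do to the result.** One State makes up 18/30 = 0.60 of one arm and 12/30 = 0.40 of the other. With equal numbers of providers per facility and no adjustment, the arm contrast moves by (0.60 − 0.40) x the State gap in competence. The article gives no gap. Over an assumed range:
- gap 0: shift 0;
- gap 15 points: 0.20 x 15 = 3 points;
- gap 25 points: 0.20 x 25 = 5 points.

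The target difference in Sample size is 20 points. The sign of the shift is random.

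**The case against.** Four things can be said for the plan.

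First, a reader might infer from the wording that whole strata are assigned to an arm, which would confound arm with level of care. The document does not support this. It names the facility as the unit, and 1:1 permuted blocks make sense only for facilities within strata; nine whole strata could not be split 1:1 in any case. The phrase is loose and needs correcting, but it does not describe the design.

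Second, a reader might call the State imbalance a bias. It is not. Facility randomisation that omits State is still valid and balances State in expectation. What is lost is precision and the assurance of balance in the one allocation that is drawn.

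Third, the size in points rests on a State gap for which the article offers nothing; Study setting gives only populations and zones. If the States perform alike, the shift is near zero. This stands.

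Fourth, the analysis partly covers the problem, because location is checked for balance and imbalanced facility characteristics are adjusted for. This also stands in part. But the rule is triggered by the data and does not name State.

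The matching sentence may simply restate the grouping by zone and level, and the stated model is an unmatched one. That makes a matched-pair design unlikely, but the sentence remains unexplained. A condensed article may leave procedural detail to the full protocol. The mismatch between 9 and up to 18, however, is between two statements the article itself makes.

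**Conclusion.** The point holds in limited form. The stated nine strata agree with the eligibility section only if zones of different States are pooled. As written, State plays no part in the allocation, and the intended balance in location is not secured at State level. With 30 facilities per State assumed, an 18:12 or worse split has a probability of about 20% (17 to 20% over the State splits examined). The consequence is chance imbalance and some loss of precision, partly covered by the planned adjustment. The 3 to 5 point shift applies only with an assumed State gap of 15 to 25 points, an 18:12 split and no adjustment, so it illustrates the possible size and is not an estimate. The wording about randomising strata and about matching is unclear and should be reconciled; neither phrase shows that the trial allocates by stratum or uses a matched design.

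**What to change.** **If allocation has not been done:** include State among the stratification factors, for example State x level (2 x 3 = 6 strata), or State x zone x level with sparse cells collapsed, and correct the number of strata to match. State that facilities are randomised 1:1 in permuted blocks within strata.

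**If allocation has been done** (the trial was registered retrospectively, so this is possible): report the scheme actually used, including the real strata.

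**In either case:** say whether any matching took place and on what, and reword the sentence that speaks of randomising each stratum. Prespecify State and the stratification factors (at least level of care) as fixed terms in every arm comparison, in place of adjusting only for characteristics found imbalanced at baseline.

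**Cost:** a few sentences of protocol text and a few extra model terms. With State x level alone, zone within State is no longer forced to balance. With all 18 cells, the average is 3.3 facilities per cell, which is why sparse cells would need collapsing.
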